## Abstract

**Background:**

Problematic gaming and broader digital media-related family difficulties are increasingly encountered not only in specialist mental health services but also in everyday municipal support services. Sweden’s new Social Services Act strengthens municipalities’ responsibility to provide early, accessible, and knowledge-based support, creating both an opportunity and an obligation to evaluate whether structured, family-centered programs can be delivered effectively in this setting. The present protocol therefore addresses whether S-FAME, a social-services adaptation of the FAME model, can be implemented and evaluated as a low-threshold, preventive support within Swedish municipal social services. This randomized controlled trial aims to evaluate the effectiveness, implementation feasibility, acceptability, and health economic consequences of S-FAME. Specifically, the trial will test whether S-FAME reduces child screen-related problems and improves parent-child relationship outcomes compared with treatment as usual followed by access to a brief parent-focused digital intervention, and will examine whether changes in parenting behaviors mediate changes in child outcomes.

**Methods:**

Families with children aged 10–14 years who seek municipal social services support because of digital media use (including gaming and excessive social media use) or related family conflict will be recruited from participating municipalities. Atleast176 families will be randomized in a 1:1 ratio to immediate S-FAME or a condition consisting of regular support from social services during the study period and subsequent access to P-FAME, a three-session online intervention for parents. S-FAME is delivered by trained municipal staff and retains selected family-centered principles from FAME while adapting content, referral pathways, risk management, and implementation procedures to preventive social services. Quantitative outcomes will be collected at baseline, postintervention, and 1-month follow-up. Qualitative interviews and focus groups will explore family and staff experiences, implementation fit, and the balance between fidelity and local adaptation. A health economic evaluation will estimate implementation costs and potential cost-effectiveness from municipal and broader societal perspectives.

**Discussion:**

Recruitment is planned to begin in February 2026 and end in December 2026. Final analyses of trial outcomes, qualitative implementation data, and health economic data are planned for the first quarter of 2027.

**Trial registration:**

ClinicalTrials.gov NCT07245862 approval date April 20, 2026 (ongoing trial).

**Supplementary Information:**

The online version contains supplementary material available at 10.1186/s40359-026-05302-x.

## Introduction

Children’s digital media environments have become embedded in everyday development rather than representing a discrete or exceptional exposure. Gaming, social networking, streaming, messaging, and school-related digital activities now intersect with peer relationships, leisure, learning, sleep routines, and family life. A scientific rationale for intervention therefore requires a distinction between high-frequency use and clinically or socially problematic use. In ICD-11, gaming disorder is defined by impaired control over gaming, increasing priority given to gaming over other activities, and continuation or escalation despite negative consequences, with sufficient severity to impair personal, family, social, educational, occupational, or other important functioning, usually over at least 12 months [1]. In community and preventive settings, however, families often seek support before a child meets diagnostic criteria—presenting instead with recurrent conflict, disrupted routines, sleep problems, emotional distress, reduced participation in offline activities, or impaired school and family functioning [2, 3].

Recent population and public health data indicate that problematic digital media use is relevant beyond specialist psychiatric services. In the WHO Health Behaviour in School-aged Children (HBSC) study across Europe, central Asia, and Canada [4], problematic social media use among adolescents increased from 7% in 2018 to 11% in 2022, and 12% of adolescents were classified as being at risk of problematic or risky gaming; boys were more likely than girls to be at risk of problematic gaming, whereas girls reported higher rates of problematic social media use [4]. Swedish reports similarly show that digital media are deeply integrated into child and adolescent lives, with widespread use of social media and gaming among young people [5, 6]. These patterns do not imply that ordinary digital media use is inherently harmful. Rather, they underscore the need to identify the subgroup of families for whom digital media routines have become difficult to regulate and are associated with distress, impairment, or escalating parent-child conflict.

The Swedish Public Health Agency has emphasized that children’s digital media use should be understood in relation to sleep, physical activity, schoolwork, social relationships, and family routines rather than as screen time alone [2, 3]. This orientation is consistent with developmental and family-systems perspectives. According to transactional models of development [7, 8], child behavior and the family environment influence each other over time, with each shaping and being shaped by the other across developmental contexts. In the context of digital media use, parental monitoring, boundary setting, emotional warmth, family communication, and conflict may shape children’s media habits, while persistent screen-related problems may also increase parental stress and undermine relationship quality. Systematic reviews support this bidirectional and contextual interpretation: poorer parent-child relationship quality, negative family dynamics, and lower parental involvement have been associated with problematic gaming and problematic internet use, whereas positive parenting and supportive family dynamics appear protective [9, 10]. Longitudinal work further suggests that family dysfunction and problematic gaming may reinforce one another across time [11]. These bidirectional dynamics are particularly relevant for sleep, school functioning, and peer relationships, which may serve as both antecedents and consequences of problematic digital media use within the family system [11].

Although preventive programs targeting problematic digital media use are on the rise, they generally focus on the child alone, without considering the broader social contexts in which the child and their behaviors are embedded. A family-centered intervention is therefore theoretically justified: the target is not only the child’s digital behavior but also the routines, communication patterns, and parenting practices through which digital media use is negotiated. Our previous clinical studies on problematic gaming have shown that both children and parents describe the parent-child relationship as central when gaming becomes problematic, and that families request support that includes parents rather than focusing exclusively on the child [12–17].

The original FAME program was developed for CAMHS (Child and adolescent psychiatry health services) as a group-based, family-centered intervention for children and adolescents with problematic gaming or excessive screen use and their parents aim at. It was informed by theoretical and empirical knowledge of parenting and child and adolescent development, findings from an earlier randomized trial of individual treatment for youth gaming problems, and interviews with parents about their support needs. FAME combines psychoeducation, cognitive restructuring, social-emotional learning, and parenting skills through an individual preparatory meeting followed by four group sessions for children and parents. The sessions address the positive and negative aspects of screen use and boundary setting, links between thoughts, feelings, and behaviors, conflict triggers and emotion regulation, and sleep hygiene [18].

However, the pathway through specialist child and adolescent psychiatry may be too narrow for families who experience screen-related conflict but do not require, or are not ready to seek, psychiatric treatment. This creates a prevention and service gap between general public health advice and specialist clinical intervention [18]. Together, these findings underscore the need for an intermediate, family-centered support pathway that is accessible, nonstigmatizing, and grounded in evidence. Although preventive programs targeting digital media use are emerging [10, 14], they generally focus on the child alone and do not address the broader family context. The present study is situated in that gap—between universal public health messaging and specialist psychiatric care—by evaluating S-FAME (where S stands for Social services) as a structured, family-centered program delivered within Swedish municipal social services.

To address this gap, we developed S-FAME, a family-centered program adapted for preventive social services. S-FAME is designed as a low-threshold municipal social services intervention for families with children aged 10–14 years who experience problematic gaming, excessive screen use, or broader digital media-related family difficulties. This setting is scientifically and practically important. Sweden’s new Social Services Act, effective from July 2025, emphasizes preventive, accessible, and knowledge-based social services, and gives municipalities greater scope to provide some interventions without an individual needs assessment [19, 20]. Swedish municipal social services already deliver a range of evidence-based parenting support programs, making them a natural setting for a family-centered digital media intervention. Evaluating S-FAME in this context will therefore address not only whether a family-centered model can improve child and family outcomes, but also whether such support can be implemented as an early, nonstigmatizing, and scalable municipal service.

## Objectives

The overarching aim is to evaluate S-FAME as an adapted, municipal social services intervention for families with children aged 10–14 years experiencing digital media-related conflict, problematic gaming, or excessive screen use.

The specific research questions are as follows:

Does S-FAME reduce child digital media-related problems compared with the comparator pathway?Does S-FAME improve parenting practices, parent–child communication, and perceived warmth and conflict in the family?Are changes in parenting behavior and family interaction associated with changes in child screen-related outcomes?Is S-FAME feasible, acceptable, and appropriate for delivery by municipal social services staff?What implementation conditions support or hinder delivery, fidelity, family engagement, and scale-up?What are the costs and potential cost-effectiveness of S-FAME from municipal and societal perspectives?What are the experiences of children and families who participate in S-FAME, and how do they understand and engage with the support offered through social services?

### Methods

This protocol was prepared in accordance with the Standard Protocol Items: Recommendations for Interventional Trials (SPIRIT) 2013 statement [21]. A completed SPIRIT checklist is provided as Appendix X Relevant SPIRIT items are addressed throughout the Methods section below.

### Study design

This protocol describes a 2-arm, parallel-group randomized controlled trial with embedded implementation, qualitative, and health economic components. Families will be randomized to immediate S-FAME or to a comparator pathway consisting of treatment as usual during the study period and later access to P-FAME (Parental- Family-Centered Treatment Program for Problematic Gaming and Excessive Screen Use in a Clinical Child and Youth Population), a brief online parent intervention. Six social services units across participating municipalities have endorsed the project and will support implementation procedures.

### Recruitment and eligibility

Families will be recruited through participating municipal social services when parents or children seek support for repeated digital media use conflict, impaired routines, parental concern, or child functioning problems. The target group is families who experience digital media-related difficulties severe enough to seek structured support from social services. Based on power analyses appx 176 participants will be required to detect a small effect size (d = 0.03), accounting for potential attrition. Eligible families must include a child aged 10–14 years; at least one parent or legal guardian willing to participate (note: both child and parent participation is required for S-FAME delivery); reported concern related to gaming, social media use, other digital media activities, or screen-related family conflict; and sufficient Swedish language ability to participate in sessions and complete measures. Families will be excluded when acute safeguarding concerns, severe psychiatric instability, ongoing crisis, or another service need makes participation in a group-based preventive intervention inappropriate.

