### Randomization and control group

After consent, eligibility confirmation, and baseline assessment, families will be randomized in a 1:1 ratio to immediate S-FAME or the comparator pathway. Allocation will be concealed from the assigning researcher until after eligibility confirmation and baseline assessment, using a centralized randomization procedure (e.g., sealed envelopes or web-based allocation). The control group will receive regular support from social services (treatment as usual) during the study period, reflecting ordinary municipal routines available to families. After the study period, families in the control group will be offered P-FAME, a three-session online intervention for parents. This delayed parent-focused offer is included for ethical and practical reasons and should be described consistently as part of the control condition rather than as the same intervention as S-FAME.

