### Statistical analysis

Analyses will be conducted using SPSS, Stata, R, Mplus, AMOS, or equivalent software as appropriate for the final model specification. Descriptive analyses will summarize recruitment, baseline characteristics, retention, attendance, missingness, and adverse events. The primary effectiveness analysis should follow the intention-to-treat principle. Between-group change over time will be estimated using regression-based models or mixed-effects models that account for repeated measurements and baseline values. If families are nested within groups, facilitators, or municipalities, clustering will be considered in the model structure or sensitivity analyses.

Mediation or mechanism analyses may test whether changes in parenting practices, boundary setting, warmth, or conflict explain changes in child digital media-related outcomes. These analyses should be presented as exploratory unless the sample size and temporal ordering are sufficient for confirmatory causal mediation. Missing data will be examined, and multiple imputation or full-information maximum likelihood will be considered when assumptions are plausible. Qualitative data will be analyzed using reflexive thematic analysis [31] with procedures to support credibility, such as team coding, analytic memos, and discussion of discrepant cases.

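### The stated target effect of d = 0.03 cannot be detected with 176 families, and d = 0.3, if that was meant, is reached only under adjustment assumptions the article does not state

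*Protocol article*

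**What the plan says.** Under Recruitment and eligibility, the protocol article says "Based on power analyses appx 176 participants will be required to detect a small effect size (d = 0.03), accounting for potential attrition". The Methods part of the abstract says "Atleast176 families will be randomized in a 1:1 ratio to immediate S-FAME", and Randomization and control group says that "families will be randomized in a 1:1 ratio to immediate S-FAME or the comparator pathway". Together these make 176 the total over both arms, 88 per arm, with the family as the randomized unit. One place counts participants and the other families.

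The article gives no alpha, power, test, attrition rate, baseline correlation or clustering allowance for this calculation. Outcomes and measures lists two assessments after baseline. Statistical analysis plans "regression-based models or mixed-effects models that account for repeated measurements and baseline values" and says clustering by group, facilitator or municipality will be considered.

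**The concern.** A standardized difference of 0.03 is a tenth of what a trial of this size could plausibly aim for, so at least one of the two figures in the sentence must be wrong. A slipped decimal (0.3) is the obvious repair. It does not settle the matter, because 176 is then a familiar per-arm number rather than a total.

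What is at stake is how the result is read. If the article is taken at its word, a null finding could be read as ruling out a small effect when the design may not be able to do so. The health economic plan also depends on the main comparison, because the incremental cost-effectiveness analysis is conditional on a meaningful between-group difference.

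**Working it through.** **Inputs from the article:** d = 0.03; 176 in total; 1:1 allocation, so 88 per arm; attrition said to be included (rate not given); two follow-ups.

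**Assumed, because not stated:** two-sided 5% and 80% power, with one-sided 5% and 90% power also tried; attrition of 0 to 20%; baseline correlation r of 0 to 0.8; no clustering.

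**Formulas** (SD = 1)
- Normal approximation, per arm: n = 2(1.960 + 0.842)² / d² = 15.70 / d². The exact two-sample t-test was solved alongside.
- Noncentrality for power with n per arm: d·√(n/2).
- Variance factor for baseline adjustment, one follow-up: 1 − r².
- Variance factor for baseline adjustment, mean of two follow-ups, all correlations equal to r: (1 + r)/2 − r².

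**Step 1. The printed claim, d = 0.03**
- n = 15.70 / 0.0009, about 17,442 per arm; the t-test gives 17,443.
- With 88 per arm the noncentrality is 0.03 × √44 = 0.20, and the t-test power is 5.4%, barely above the false-positive rate.
- The least demanding unadjusted variant tried (one-sided 5%, 80% power) still needs 27,480 in total.
- A single-follow-up baseline correlation of 0.99 still needs 696 in total.

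The printed figure is not reproduced.

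**Step 2. Reading d as 0.3, unadjusted**
- n = 15.70 / 0.09 = 174.4, so 175 per arm; the t-test gives 175.4, so 176 per arm, or 352 in total before attrition.
- One-sided 5% with 80% power gives 276 in total; two-sided 5% with 90% power gives 468. No unadjusted variant tried gives 176 as a total.
- Power with 88 per arm: noncentrality 0.3 × √44 = 1.99, power 51%.
- With 20% attrition (70.4 per arm): noncentrality 0.3 × √35.2 = 1.78, power 42%.

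**Step 3. Reading d as 0.3, with the adjustment the analysis plans** (normal approximation, 88 per arm randomized)

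| Analysis | r | Variance factor | Attrition | Power at d = 0.3 |
|---|---|---|---|---|
| One follow-up | 0.5 | 0.75 | 0% | 63% |
| One follow-up | 0.7 | 0.51 | 0% | 80% |
| One follow-up | 0.75 | 0.44 | 10% | 81% |
| One follow-up | 0.8 | 0.36 | 20% | 84% |
| Mean of two | 0.5 | 0.50 | 0% | 80% |
| Mean of two | 0.6 | 0.44 | 10% | 81% |

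So 176 in total can support d = 0.3, but only if correlations of this order were assumed. Any clustering would raise the required number.

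**Step 4. What 88 per arm detects at 80% power** (t-test, two-sided 5%, no clustering)
- Unadjusted: d = 0.42 with no attrition, 0.48 with 20% attrition.
- One follow-up, r = 0.5, multiplying by √0.75 = 0.866: 0.425 × 0.866 = 0.37 with no attrition, 0.476 × 0.866 = 0.41 with 20% attrition.

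**The case against.** The strongest reply is that 0.03 is a typing error for 0.3 and that the calculation behind 176 used the planned analysis. The article foresees baseline adjustment and two follow-ups, and Step 3 shows that moderate to high correlations bring 88 per arm to about 80% power at d = 0.3, even with some attrition. This stands as a possibility. It does not rescue the printed figure, and the article states no correlation that would let a reader confirm it.

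A reader might infer more than the article supports, in three ways.

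- **That 176 is a per-arm result mistakenly used as the total, so the trial has half the families it needs.** The match with the unadjusted t-test at d = 0.3 is exact, which makes this plausible, but another reading also fits. At d = 0.45 the t-test needs 79 per arm, 158 in total, and 158 / 0.9 = 175.6, so 176 with 10% attrition. That keeps 176 as a total with attrition included, as the text says, although 0.45 would not usually be called small. The article confirms neither reading.
- **That no attrition allowance can be inside 176.** This follows only if the per-arm reading is right. The sentence itself says "accounting for potential attrition".
- **That 176 counts children and parents separately, leaving 44 families per arm.** The abstract and the randomization section both refer to families, so this is more likely loose wording than a different design.

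**Conclusion.** The point holds in this form. The claim that 176 detects d = 0.03 is wrong: power is about 5%, and about 17,443 per arm would be needed. This does not depend on the choice among standard alpha, power or adjustment assumptions.

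The rest is conditional. If d = 0.3 was meant, 176 in total is half the 352 required by an unadjusted two-sided 5% test at 80% power, before attrition. It is about enough under the baseline-adjusted, repeated-measures assumptions in the table. The article therefore does not support a flat statement that the trial cannot detect d = 0.3. Nor does it support describing the trial as powered for a small effect. Which applies depends on inputs that only the sponsor can supply, and clustering would move all of these figures in the unfavourable direction.

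This needs correcting before results are known, because it is the only justification given for the trial's size.

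**What to change.** No enlargement of the trial is asked for. In Recruitment and eligibility:

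1. Replace d = 0.03 with the effect that 176 families can detect, and state the alpha, sidedness, power, test, baseline correlation, number of follow-ups used, attrition rate and clustering allowance behind it. If a baseline-adjusted calculation for d = 0.3 exists, report it with its assumed correlation.
2. Confirm that 176 is the total over both arms.
3. Write families both there and in the abstract.
4. Drop the description of the effect as small unless the stated assumptions support it. If they do not, say that a null result does not exclude d = 0.3.

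The Step 4 values (0.42 and 0.48 unadjusted, 0.37 and 0.41 adjusted at r = 0.5) are for reference only. They rest on assumed alpha, power, attrition and correlation, contain nothing for clustering, and should not be copied in unless the sponsor adopts those assumptions.

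The cost is a few sentences in the article, with the registry entry aligned if it carries the same figure. The stated sensitivity will look less favourable, but no design element changes.

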### Randomization and control group

After consent, eligibility confirmation, and baseline assessment, families will be randomized in a 1:1 ratio to immediate S-FAME or the comparator pathway. Allocation will be concealed from the assigning researcher until after eligibility confirmation and baseline assessment, using a centralized randomization procedure (e.g., sealed envelopes or web-based allocation). The control group will receive regular support from social services (treatment as usual) during the study period, reflecting ordinary municipal routines available to families. After the study period, families in the control group will be offered P-FAME, a three-session online intervention for parents. This delayed parent-focused offer is included for ethical and practical reasons and should be described consistently as part of the control condition rather than as the same intervention as S-FAME.

